# 1. SUMMARY OF THE STUDY

| **Title** | Lymphocytic enteritis with negative coeliac serology and clinical and histological response to a gluten-free diet: double-blind randomized clinical trial with rechallenge of gluten vs. placebo. | |
| --- | --- | --- |
| **Study code** | EL-DSG/07/2011 | |
| **Objectives** | To demonstrate hypersensitivity to gluten in patients with lymphocytic enteritis, and clinical response and histology of a gluten-free diet despite the presence of IgA negative tissue anti-transglutaminase antibodies. | |
| **Treatment** | Sachets with gluten (10 g) or placebo (maltodextrin: 10 g): 1 sachet every 12 hours. | |
| **Study design** | Prospective, randomized, double-blind, placebo-controlled, with parallel groups of gluten rechallenge vs. placebo, for 24 weeks, in patients following a gluten-free diet.   - Group A: Powdered gluten (10 g every 12 hours) - Group B: Placebo (10 g every 12 hours)   Determination of digestive clinical state, adherence to diet, coeliac serology, histology, flow cytometry, and tissue anti-transglutaminase antibodies in intestinal mucus membrane, at baseline and after gluten rechallenge or placebo (whether clinical digestive symptoms reappear at 4 or 12 weeks, or at the conclusion of the study at 24 weeks). | |
| **Study population** | Inclusion criteria:  1. Signed informed consent  2. Age 18 or older  3. Confirmed histological diagnosis of lymphocytic enteropathy (LE)  5. Coeliac-positive genetic study (HLA-DQ2 and/or HLA-DQ8)  6. Negative coeliac serology  7. Complete clinical and histological response to gluten-free diet  8. Initial clinical signs with or without extra-intestinal manifestations | |
|  | Exclusion criteria:  1. Inability to adhere to the scheduled visits or other protocol requirements, in the judgement of the investigator  2. Participation in a clinical trial in the previous 30 days, simultaneous participation in a trial, or prior participation in the present study  3. History of gluten-sensitive enteropathy with villous atrophy or positive serology  4. Lymphocytic enteropathy or initial response to gluten-free diet but following a normal diet at the time of selection | |
| **Sample size** | 20 patients | |
| **Length of treatment** | 24 weeks | |
| **Primary efficacy variables** | Reappearance of clinical digestive signs and histological recurrence | |

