**6.3. EXPECTED NUMBER OF SUBJECTS**

The estimated sample size is 20 patients (10 for each treatment group) who will be evaluated on the basis of intention to treat.

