**8. DEVELOPMENT OF TRIAL AND ASSESSMENT OF RESPONSE**

**8.1. PRINCIPAL AND SECONDARY ASSESSMENT VARIABLES**

**Efficacy criteria**

- Primary efficacy evaluation variable: Reappearance of clinical digestive signs (24 weeks)
- In addition, secondary efficacy variables will be evaluated:
  - Clinical signs at 4 weeks
  - Clinical signs at 12 weeks
  - Flow cytometry to measure percentage of lymphocytes CD3+ gamma-delta+ and CD3- in intestinal mucus membrane
  - Assessment of IgA tissue anti-transglutaminase antibodies in the intestinal mucus membrane
  - IgA tissue anti-transglutaminase antibodies in serum and anti-endomysium antibodies
  - Quality of life according to the GIQLI questionnaire.
  - Histological changes on biopsy in the distal duodenum

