**8.3. DESCRIPTION OF METHODS USED TO ASSESS RESPONSE**

Clinical response will be measured with analogue visual scales ranging from 0 to 100, administered at baseline and at each visit up to 6 months, for symptoms of abdominal pain, abdominal swelling, diarrhea, and flatulence (total score 0 to 400 points) (Appendix 6).

Patient quality of life will be evaluated in the first visit and the last (at 6 months, or at early withdrawal) using the GIQLI questionnaire (Gastrointestinal Quality of Life Index), which has been shown to yield valid, reliable scores for the detection of significant clinical changes in the lives of patients regarding their health (Eypasch E et al. Gastrointestinal Quality of Life Index: development, validation and application of a new instrument. Br J Surg 1995; 82:216-22; Quintana JM et al. Translation and validation of the Gastrointestinal Quality of Life Index (GIQLI). Rev Esp Enferm Dig 2001; 93:693-706) (See Appendix 3).

At the first visit and the last (or at early withdrawal from the study) a distal duodenal biopsy will be drawn for histological study, and evaluation of tTG deposits and lymphocytic sub-populations (using flow cytometry) will be made.

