**8.4. WITHDRAWAL CRITERIA**

Any patient may withdraw from the study at any time without incurring any personal penalty and without the need for explanation. Withdrawal must be noted in the CRF when it occurs, along with the results to date and the reason(s) for withdrawal, if given.

The investigator may also withdraw a patient from the study upon consideration of the risks and benefits thereof, and determination that the former outweigh the latter with continued participation. The CRF must reflect the date and main cause for the withdrawal, as well as any further observations that may be made at the time of withdrawal. Among the reasons for withdrawing a patient early from the study are the following (the main reason should be indicated):

• Lack of efficacy of treatment, e.g.:

– Progression of the illness under study in comparison to baseline.

(in the six weeks following).

– The need to administer a concomitant medication that is prohibited in the treatment of the illness under study.

• Intolerable adverse events.

• Lack of patient cooperation, e.g.:

– Patient request.

– Lack of therapeutic compliance or failure to carry out visits according to the agreed calendar.

– Technical or logistical reasons (e.g., change of patient residence).

– Pregnancy or breast-feeding, either existing or planned.

• Others (must be noted), e.g.:

– Diagnosis different from that of the study.

All patients withdrawing early from the study must be seen within 7 days of the last administration of the medicine used in the study. This final visit is to be duly recorded in the CRF.

The investigator will continue to observe all patients withdrawing early from the study as a result of intolerable adverse events until the findings have been resolved.

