**13. STATISTICAL ANALYSIS**

The calculation for the sample size is based on the main variable of efficacy—that is, the rate of recidivism at 6 months. On the basis of results of previous studies it was determined that the rate of recidivism with the reintroduction of gluten would be 80%, and with placebo 20%. Assuming a 10% patient drop-out rate, an alpha value of 5%, and statistical power (beta) of 80%, for a bilateral test it was calculated that 10 patients would be needed for each patient group (bearing in mind that analyzing the results would require a Chi-square test with Yates correction). The total number, then, is 20 patients.

Excluded from this analysis are those subjects presenting significant departures from the protocol.

All of the evaluations of the primary and secondary variables, both of efficacy and of safety, are understood in the exploratory sense (alpha=0.05, bilateral).

The Chi-square test with Yates correction will be used for independent groups and the Fisher exact test for qualitative variables. For intergroup comparison of the quantitative variables, the Student-t test will be used for parametric variables, and the Mann-Whitney U-test for non-parametric variables.

The finding of values for differences of p less than 0.05 will be considered significant. The rates for clinical remission between treatment groups will be expressed proportionally with the corresponding bilateral interval of confidence of 95%, as an estimation of therapeutic effect.

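### Section 6.3 promises intention-to-treat but Section 13 excludes protocol deviators, and nothing stops that exclusion from removing patients who have relapsed

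*Protocol*

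**What the plan says.** Two sections of the protocol define who is analysed.

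- Section 6.3 gives 20 patients, 10 per group, "who will be evaluated on the basis of intention to treat".
- Section 13, immediately after the paragraph that sizes the trial on the main efficacy variable, states: "Excluded from this analysis are those subjects presenting significant departures from the protocol". It does not define a significant departure, name a per-protocol set, or say which population is primary.

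Three other places bear on the point.

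- Section 8.1 makes the return of digestive symptoms, at 24 weeks, the primary variable. The Summary brings the final determinations forward, depending on "whether clinical digestive symptoms reappear at 4 or 12 weeks, or at the conclusion of the study at 24 weeks".
- Section 8.4 lets the investigator withdraw a patient on a judgement of risk and benefit. It introduces its list with "Among the reasons for withdrawing a patient early from the study are the following". The list includes "Progression of the illness under study in comparison to baseline" and also "Lack of therapeutic compliance or failure to carry out visits according to the agreed calendar".
- Section 8.3 plans data at exit: "At the first visit and the last (or at early withdrawal from the study) a distal duodenal biopsy will be drawn". Section 8.4 adds a visit within 7 days of the last dose.

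**The concern.** The two statements cannot both govern the primary comparison. Intention-to-treat keeps every randomised patient; the Section 13 sentence removes some of them after randomisation.

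The design makes this more than a wording fault. This is a rechallenge trial, and the event it counts is symptoms coming back. A patient whose symptoms return may stop the sachets or miss a visit. Section 8.4 lists both as reasons for withdrawal, and either could be judged a significant departure. No sentence says that such a patient's relapse is still counted. With 10 patients per arm, a couple of exclusions can settle the result.

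**Working it through.** **Inputs.** From Section 13: relapse 80% on gluten and 20% on placebo, two-sided alpha 5%, stated power 80%, 10% dropout, chi-square with Yates correction; Fisher's exact test is also named. From Sections 5.1 and 6.3: 1:1 allocation, 10 per group. The protocol gives no exclusion fraction, so 25% and 50% of relapsers are assumptions used to show a range.

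**The plan's own figure.** With pooled variance and neither Yates nor dropout:

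n = [1.96·√(2·0.5·0.5) + 0.8416·√(0.8·0.2 + 0.2·0.8)]² / 0.6² = 9.6, so 10 per group.

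This matches the printed number. With the continuity correction the same method gives 13, and with 10% dropout 13/0.9 = 14.4, so 15. Exact power at 10 per group is 63.5% with either Yates or Fisher. That shortfall is a separate matter; it is stated here only because 63.5%, not 80%, is the baseline below.

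**Effect on the planned result.** For gluten a relapsed and c not, placebo b relapsed and d not, and N the total, the Yates statistic is N(|ad − bc| − N/2)² divided by the product of the four margins. The 5% critical value is 3.84.

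- 8/10 v 2/10: 20·(60 − 10)² / (10·10·10·10) = 5.00
- 7/9 v 2/10: 19·(52 − 9.5)² / (9·10·9·10) = 4.24
- 6/8 v 2/10: 18·(44 − 9)² / (8·10·8·10) = 3.45
- 8/8 v 2/10: 18·(64 − 9)² / (8·10·10·8) = 8.51

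| Excluded from gluten arm | Analysed | Fisher p | Yates p |
|---|---|---|---|
| nobody | 8/10 v 2/10 | 0.023 | 0.025 |
| one relapser | 7/9 v 2/10 | 0.023 | 0.040 |
| two relapsers | 6/8 v 2/10 | 0.054 | 0.063 |
| two non-relapsers | 8/8 v 2/10 | 0.001 | 0.004 |

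**Effect on power.** Suppose each relapser is excluded with probability q. The relapse rate among those analysed becomes p(1 − q)/(1 − pq).

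- Gluten: 0.60/0.80 = 75% at q = 0.25; 0.40/0.60 = 67% at q = 0.50.
- Placebo, if the exclusion applies there too: 0.15/0.95 = 16% and 0.10/0.90 = 11%.

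Power by exact enumeration over all outcomes and exclusions:

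| Relapsers excluded (assumed) | Arms affected | Fisher | Yates |
|---|---|---|---|
| none | – | 64% | 64% |
| 25% | both | 63% | 56% |
| 50% | both | 51% | 40% |
| 25% | gluten only | 54% | 49% |
| 50% | gluten only | 35% | 26% |

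**The case against.** The best defence is that the protocol never equates relapse with a departure. Section 8.4 permits withdrawal for progression but does not require it, and provides for it with an exit visit and biopsy. A patient who leaves by that route has followed the protocol. This stands. A reader might infer that relapse itself leads to exclusion; the documents do not support that. What remains is the indirect route, from symptoms to missed sachets or visits to a judgement of significant departure. That is plausible and unguarded, but not stated.

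Other stronger readings also fail.

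- One exclusion does not overturn the planned result; two relapsers are needed.
- The bias need not run towards no effect. Removing non-compliant gluten patients who did not relapse inflates the difference.
- Under blinding, exclusion driven by symptoms would be expected in both arms. The gluten-only power figures are therefore the harsher assumption, and with Fisher the two-arm loss at 25% is almost nil.
- The protocol does not say that departures may be classified after unblinding; it is silent on timing, and an analysis plan not at hand may settle it.
- Nor does it say that relapse is read only as status at week 24. Reappearance reads more naturally as an event by then, and the Summary brings the final assessment forward when symptoms return.

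Section 13 also calls every evaluation exploratory. That softens a pass-or-fail reading, but the same section declares p below 0.05 significant, and Section 4.2 aims to demonstrate hypersensitivity. An analysis plan could define departures, but it could not honour both Section 6.3 and Section 13 for the same analysis.

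**Conclusion.** The contradiction is explicit and needs no assumption: the population for the primary comparison is undetermined. That the exclusion may depend on outcome is a possibility the protocol leaves open, not something it prescribes.

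The choice of population can change the conclusion. At the planned result, losing two gluten relapsers moves Fisher p from 0.023 to 0.054, while losing two gluten non-relapsers moves it to 0.001. If a quarter to a half of relapsers were excluded, power would fall from 64% to between 63% and 51% (Fisher) or 56% and 40% (Yates) with both arms affected, and to as little as 35% or 26% with gluten only. These power figures rest on the protocol's 80% and 20% rates and on assumed exclusion fractions. Because the direction of bias is not fixed, it cannot be allowed for afterwards; the rule has to be set in advance. This should be corrected before the analysis.

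**What to change.** Replace the exclusion sentence in Section 13 with text to this effect, so that it agrees with Section 6.3:

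- The primary analysis includes all randomised patients in their assigned group.
- Relapse at or before early withdrawal counts as an event by week 24, and relapse is counted cumulatively at weeks 4 and 12.
- An analysis without patients who have predefined major departures, classified before unblinding, is a sensitivity analysis only.

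Carrying the exit symptom score to later visits is not needed for this. The cost is a few sentences. The exit visit and biopsy are already planned in Sections 8.3 and 8.4, so no data are added, and no withdrawal or other clinical rule changes; only how a withdrawn patient is counted.

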**5.1. RANDOMIZATION**

A 1:1 proportion will be followed in making random assignment of participants to treatment groups. Assignment will be made using a computer, and medication coded consecutively with numbers for dispensation, following a double-blind schema, in the hospital pharmacy at the admission of each subject to the study.

On day 1 of the study each randomized patient will receive a participant number which will also be used for his or her medication. This randomized number will be associated with a specific treatment.

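### Section 13 puts adverse events under the same p<0.05 rule as efficacy; at 10 per arm an excess of 4 v 0 patients would be labelled not significant, so counts and intervals are the better report (minor)

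*Protocol*

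**What the plan says.** Section 13 sets one reading rule for everything that is evaluated: "All of the evaluations of the primary and secondary variables, both of efficacy and of safety, are understood in the exploratory sense (alpha=0.05, bilateral". Safety is named in that sentence. For categorical data the tests are: "The Chi-square test with Yates correction will be used for independent groups and the Fisher exact test for qualitative variables". The threshold follows without any exception for safety: "The finding of values for differences of p less than 0.05 will be considered significant". The only interval estimate promised in Section 13 is a two-sided 95% interval for clinical remission by treatment group. None is promised for adverse events.

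Section 6.3 gives the size: "The estimated sample size is 20 patients (10 for each treatment group". Section 13 derives it from relapse alone, assuming that "the rate of recidivism with the reintroduction of gluten would be 80%, and with placebo 20"%.

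On safety itself, Section 8.1 asks for a registry of side effects and defines no comparative safety endpoint. Section 9.1.3.1 expects no adverse events from either supplement and gives no rate. Section 9.2 has each event recorded individually, with severity, seriousness and WHO causality, and has serious events reported within 24 hours.

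**The concern.** The sample was chosen to detect a 60-point difference in relapse. The same threshold is then applied to adverse events, where a much smaller excess would deserve attention. In a sample of this size a p<0.05 rule is a coarse filter for harm: a sizeable imbalance can fail it, and Section 13 specifies no other between-arm summary that would show how large the imbalance might be.

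At stake is how the safety table reads. Patients enter in complete clinical and histological response (Section 6.1, criterion 7), and half are then given gluten. If an adverse event occurs in four gluten patients and no placebo patient, the stated rule labels the difference not significant. Since Section 9.1.3.1 expects no adverse events, that label could be taken as confirmation, although the data would point the other way.

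**Working it through.** **Inputs.** 10 patients per arm (Sections 6.3 and 13), 1:1 allocation (Section 5.1), two-sided alpha 0.05, Yates-corrected chi-square or Fisher exact (Section 13). The protocol gives no adverse event rates, so every rate below is an assumption, shown over a range.

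**The plan's own figure.** The only computed figure is 10 per arm for relapse (80% v 20%, two-sided 5%, 80% power). The formula without continuity correction gives

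n = [1.96·√(2·0.5·0.5) + 0.842·√(0.8·0.2 + 0.2·0.8)]² / 0.6² = 9.6, so 10.

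This reproduces the stated figure only if both the Yates correction and the 10% dropout are left out. With Yates it is 13, and with dropout as well 13/0.9 = 14.4, so 15. That mismatch is a separate matter. The check below takes the planned 10 per arm as given.

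**Smallest significant split.**

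Fisher, two-sided, for k v 0 at equal arms: p = 2·C(10,k)/C(20,k).
- k=4: 2·210/4845 = 0.087
- k=5: 2·252/15504 = 0.033

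Yates: χ² = N(|ad−bc| − N/2)² / (product of the four margins).
- 4 v 0: 20·(40−10)² / (10·10·4·16) = 2.81, p=0.094
- 5 v 0: 20·(50−10)² / (10·10·5·15) = 4.27, p=0.039

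| Gluten v placebo (of 10 each) | Fisher p | Yates p | Difference, Newcombe 95% interval (points) |
|---|---|---|---|
| 3 v 0 | 0.21 | 0.21 | 30 (−4 to 60) |
| 4 v 0 | 0.087 | 0.094 | 40 (4 to 69) |
| 5 v 0 | 0.033 | 0.039 | 50 (12 to 76) |
| 6 v 1 | 0.057 | 0.061 | 50 (8 to 75) |
| 7 v 1 | 0.020 | 0.023 | 60 (17 to 81) |

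With two placebo events the minimum is 8 v 2, and with three it is 9 v 3. The 5 v 0 minimum is unchanged at 9, 8 and 7 per arm, so dropout or exclusions do not lower it. An uncorrected chi-square would reach p=0.025 at 4 v 0, but the protocol does not name that test.

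**Chance of p<0.05 for a true excess, 10 per arm** (exact enumeration of the possible tables; Fisher and Yates agree at this size).

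| Assumed true rates, gluten v placebo | Power |
|---|---|
| 30% v 5% | 9% |
| 30% v 0% | 15% |
| 40% v 10% | 15% |
| 40% v 5% | 24% |
| 50% v 10% | 30% |
| 40% v 0% | 37% |
| 60% v 10% | 47% |
| 50% v 0% | 62% |
| 60% v 0% | 83% |

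When the placebo rate is zero, power is simply the probability of at least 5 events in 10, which can be read from the binomial distribution.

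**Zero events.** For 0 of 10, the exact two-sided 95% upper limit is 1 − 0.025^(1/10) = 31%. An empty row in one arm of the safety table therefore excludes little.

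**The case against.** Much of the case on the other side stands.

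- **The exploratory label.** The sentence that brings safety under alpha=0.05 also calls the evaluations exploratory. That lowers the claim attached to any p value. It does not say how a non-significant safety result should be read, and the p<0.05 rule that follows has no exception.
- **No conclusion of safety is planned.** A reader might infer that the protocol will treat a non-significant difference as showing that the gluten challenge is safe. Nothing in it says so. The risk lies in how the result may be read, not in a stated decision rule.
- **Events are visible without a test.** Section 9 has each event recorded, graded and assessed for causality, whatever the p value. A 4 v 0 excess would still be in the data. What Section 9 does not settle is how the arms are compared.
- **The main harms of gluten are efficacy outcomes.** Symptom recurrence, histological change, serology and quality of life all appear among the efficacy variables in Section 8.1 (Section 1 lists histological recurrence with the primary variables). Clinical remission gets an interval. What remains is other adverse events.
- **Non-significance is not a foregone conclusion.** A reader might infer that the safety comparison is bound to be non-significant whatever the truth. The power figures rule that out: 62% for 50% v 0% and 83% for 60% v 0%. The rule is weak for moderate excesses, not for very large ones.
- **Safety tables usually belong to the SAP.** Their layout does, and its absence here is no fault. The threshold, however, is fixed in the protocol and names safety.

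**Conclusion.** The point holds as a minor one. Section 13 extends a two-sided p<0.05 rule to adverse events in a trial with 10 patients per arm, where the rule cannot be met below 5 v 0, or below 7 v 1 with one placebo event. An excess of 4 v 0, which corresponds to a difference of 40 points with an interval of 4 to 69, would carry the label not significant.

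The split thresholds follow from the stated sample size and tests alone and need no assumption about rates. The power figures, from 9% to 83%, rest on illustrative rates, because the protocol gives none. The primary result is not affected, and the protocol contains no contradiction on this point. What is open to improvement is a reading rule poorly suited to adverse events other than the recurrence outcomes.

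**What to change.** In Section 13, take adverse events out of the p<0.05 rule. Suggested wording: *Adverse events are summarised by treatment group as number of patients and number of events, by severity and relationship to the study product. For each type, the difference in proportions between groups is given with a 95% interval (for example Newcombe). Absence of a significant difference is not evidence of no harm.*

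If p values are kept, label them as descriptive flags. The interval should not become a substitute test either: at 4 v 0 the Newcombe interval excludes zero while Fisher and Yates do not reach 0.05, so it should be read for the range of differences it allows.

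The cost is a change of wording. No additional patient, visit or data item is needed, since Section 9.2 already collects severity and causality. The interval does not add power, which 20 patients cannot supply, but it shows the uncertainty that the label hides. The downside is that safety tables carry no p values, or carry them only as flags.

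### Section 13 names both Yates chi-square and Fisher's exact test for the primary 2x2 comparison; they can disagree after drop-out, and neither reaches the stated 80% power

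*Protocol*

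**What the plan says.** Protocol Section 13 sizes the trial on relapse at 6 months. It assumes that "the rate of recidivism with the reintroduction of gluten would be 80%, and with placebo 20" per cent, with two-sided alpha 5%, power 80% and 10% drop-out. It concludes that "for a bilateral test it was calculated that 10 patients would be needed for each patient group", and adds "bearing in mind that analyzing the results would require a Chi-square test with Yates correction".

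The rule for analysis comes later in the same section: "The Chi-square test with Yates correction will be used for independent groups and the Fisher exact test for qualitative variables". Nothing such as an expected cell count says when one test gives way to the other. The section calls all evaluations exploratory but still treats p below 0.05 as significant. Section 5.1 sets 1:1 allocation.

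**The concern.** The two halves of the rule do not exclude each other. One describes the design (independent groups) and the other the type of variable (qualitative). A yes/no relapse outcome compared between two parallel arms satisfies both. An analyst could run either test after seeing the data and still comply with the protocol. If the tests fall on opposite sides of 0.05, the primary conclusion depends on that choice.

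The second issue is power. Both tests are known to be conservative in small 2x2 tables. With about 10 patients per arm, the gap between the nominal 5% and the error rate actually used can be large, and that unused error is lost power.

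**Working it through.** **Inputs (Protocol Sections 13 and 5.1).** Relapse rates 0.80 and 0.20, two-sided alpha 0.05, power 0.80, drop-out 10%, allocation 1:1, 10 per arm.

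**1. The plan's own figure.** The uncorrected two-proportion formula is

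n = [1.960·√(2·0.5·0.5) + 0.842·√(0.8·0.2 + 0.2·0.8)]² / 0.6² = 9.63, so 10 per arm.

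With the continuity correction that Section 13 says the analysis requires,

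n′ = (9.63/4)·[1 + √(1 + 4/(9.63·0.6))]² = 12.7, so 13 per arm.

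After drop-out, 13/0.9 = 14.4, so 15 per arm. The stated 10 per arm matches the uncorrected test with no drop-out. It does not match the Yates test with 10% drop-out.

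**2. Do the two tests disagree?** All possible tables were enumerated. At 10 v 10 the rejection regions are identical. At 9 v 9 they differ on 8/9 v 3/9 and 6/9 v 1/9 and on the mirror images of these. For 8/9 v 3/9:

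- Yates: 18·(|8·6 − 1·3| − 9)² / (9·9·11·7) = 18·36²/6237 = 3.74, p = 0.053.
- Fisher: 2·(9·84 + 1·36)/31824 = 1584/31824, p = 0.0498.

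At 9 v 10, the table 4/9 v 0/10 gives Yates p = 0.070 and Fisher p = 0.033.

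The probability of conflict at 9 v 9 under the planned rates is 2 × 0.302 × 0.176 = 10.6%. Here 0.302 is the chance of 8 relapses in 9 at 80% (and of 1 in 9 at 20%), and 0.176 is the chance of 3 in 9 at 20% (and of 6 in 9 at 80%). At 9 v 10 the probability is 0.5%, and at 10 v 10 it is zero. Averaged over independent 10% drop-out from 10 per arm it is 5.6%. With such drop-out, all 20 patients remain with probability 0.9²⁰ = 12%.

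**3. Power and true error.** Exact power is the sum of the binomial probabilities of the rejected tables at 80% v 20%. True error is the maximum over a common relapse rate. Boschloo's test takes Fisher's p-value as its statistic and refers it to that unconditional maximum.

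| Evaluable | Yates power (max error) | Fisher power (max error) | Boschloo power (max error) |
|---|---|---|---|
| 10 v 10 | 63.5% (1.3%) | 63.5% (1.3%) | 80.5% (4.2%) |
| 9 v 10 | 67.3% (1.9%) | 67.9% (2.1%) | 72.3% (3.6%) |
| 9 v 9 | 51.9% (1.0%) | 62.5% (2.1%) | 72.1% (3.3%) |
| Averaged over 10% drop-out | 59% | 65% | 73% |

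The gain of Boschloo over Fisher is 80.5 − 63.5 = 17.0 points at 10 v 10, 72.1 − 62.5 = 9.6 points at 9 v 9, and 73.1 − 64.6 = 8.5 points averaged over drop-out. An example at 10 v 10 is 8/10 v 3/10, with Fisher p = 0.070 and Boschloo p = 0.041.

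**The case against.** The sizing sentence ties the main efficacy variable to the Yates test, so one may say that Yates was always meant for the primary analysis and the later sentence is only loosely worded. That is a fair reading, but the later sentence is the one that sets the analysis rule, and it allows Fisher equally. If Yates was intended, the plan has settled on the less powerful of the two after drop-out.

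Yates and Fisher are conventional, both stayed below 5% error at the sizes checked, and conservatism is not a contradiction. This also stands. What the plan cannot do is state 80% power and use tests that give 63.5% with complete data. The exploratory label softens the consequence, but the 0.05 threshold remains.

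Three stronger readings are tempting and unsupported:

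- A reader might infer that changing the test recovers the planned 80% with the same 20 patients. The plan's 80% is stated with 10% drop-out, where Boschloo gives 72–73%. The 80.5% needs all 20 outcomes to be known and to follow the assumed rates.
- A reader might take the 17-point loss and the 1.3% maximum error as general. They apply at 10 v 10, the very size at which Yates and Fisher never disagree.
- A reader might think that conflicting verdicts are likely. They are a minority event, at 5.6% averaged over drop-out.

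**Conclusion.** The point holds in limited form. Section 13 leaves two tests open for one primary comparison. They agree with complete data, but the chance of opposite verdicts is 10.6% at 9 v 9 and 5.6% averaged over the planned drop-out. Neither gives the stated 80% power at any of the sizes in the table. An unconditional exact test stays within 5% error, rejects every table that Fisher rejects at the sizes checked, and gains 17 points at 10 v 10 and about 8.5 points averaged over drop-out. It does not bring power back to 80% once the plan's own drop-out is applied.

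These figures assume relapse rates of exactly 80% and 20%, a binary relapse outcome at 6 months, and drop-out that is independent of outcome. If all 20 are analysed and every drop-out is counted the same way (all as relapse or all as no relapse), the rates become 82% v 28% or 72% v 18%, and Boschloo's power is 70.1%.

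**What to change.** In Section 13, replace the two-test sentence for the primary outcome with one test fixed in advance: Boschloo's two-sided unconditional exact test at alpha 0.05. Use it for the other binary variables too. Restate the power in the sample-size text with both figures: 80.5% if all 20 patients have an outcome, and about 72–73% after the planned 10% drop-out. Quoting 80.5% alone beside a 10% drop-out allowance would put a new wrong figure in the text. If 80% must hold after drop-out, the number randomised has to rise: 10/0.9 = 11.1, so 12 per arm or 24 in total with this test.

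The change of test costs a few sentences and no extra patients or visits, and standard software runs it. The small downside is that the test is less familiar to readers than Fisher's.

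Section 6.3 calls for intention to treat, while Section 13 excludes patients with significant departures from the protocol. That is a separate conflict which this change does not settle, and it should be resolved in its own right because it decides how many patients enter the test.
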